### Statistical issues

#### Sample size Calculation

The sample size calculation is based on 2 RCTs which evaluated the intra-articular injection of DPT and NS for KOA at 6 months [32, 51], assuming their therapeutic effect will remain stable for 1 year. The baseline characteristics of the two trials had comparable age, sex, BMI, and baseline WOMAC score. The mean (Standard Deviation) difference of WOMAC scores at 6 month compared with baseline status was 25.2 (20.3) points for DPT [32], and 9.53 (26.6) points for NS [51], respectively. Thus, assuming a pooled SD of 26.6, a sample size of 34 participants in each arm will have 80% power to detect a significant effect size of 0.70 in a two-sample t-test with alpha set at 0.05. Assuming 10% dropout rate, the total sample size is 76.

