#### Data analysis

We will conduct linear mixed models to investigate significant changes over time for both primary and secondary outcomes following the intention to treat principle, i.e., all available data will be analyzed according to the group they are randomly assigned. The use of LMM also provides the means to include subjects with incomplete and use all available data to assess the treatment effect over time. In this model, intervention group, time, and the interactions between the intervention groups and time will serve as predictors with duration of knee pain and number of comorbidities as covariates. Given the longitudinal nature of the clinical trial data, we assume the autoregressive covariance structure will be the best fit for the data, but the statistical fitness by using other covariance structures will also be evaluated [52].

With a clearly defined target population, effectiveness and safety outcomes, and convenient data collection procedures, our trial should realize the goal of maximizing the number of participants who are maintained on the protocol-specified intervention until the outcome data are collected. In case of a large number of outcomes and covariates with missing data, we will use multivariate imputation using chained equations (MICE) to incorporate auxiliary information about the missing data. The imputation model will include prerequisite variables in the data analysis, variables for baseline socio-economic status, and also variables that are predictors of outcomes. About 10 iterations will be conducted in each imputation process with more iterations to be considered until the chain reaches convergence [53]. Twenty completed datasets will be imputed with the use of the chain equations. The Rubin’s rule will be applied to combine the effect estimates [54]. This approach provides estimated standard errors and *P* values that incorporate missing-data uncertainty. For the patients that meet any of the exclusion criteria such as alternative treatment or severe outcome, then all subsequent longitudinal measurements since that date of the event will be excluded from the analysis.

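### The number of imputations is fixed at twenty for the case of extensive missing data, so a p-value near 0.05 could change sides with another seed; raising it is a minor, nearly free improvement.

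*Protocol article*

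**What the plan says.** All references are to the Data analysis section of the protocol article unless stated otherwise.

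- The main analysis is a linear mixed model on all available data: "The use of LMM also provides the means to include subjects with incomplete and use all available data to assess the treatment effect over time".
- MICE is a contingency: "In case of a large number of outcomes and covariates with missing data". No threshold is given.
- For that contingency the number of datasets is fixed: "Twenty completed datasets will be imputed with the use of the chain equations".
- The only stated flexibility concerns the chain: "About 10 iterations will be conducted in each imputation process with more iterations to be considered until the chain reaches convergence".
- Results are pooled by Rubin's rules: "rule will be applied to combine the effect estimates".
- The only missingness figure is under Sample size Calculation: "Assuming 10% dropout rate, the total sample size is 76".

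**The concern.** Iterations and imputations do different work. More iterations let each chain settle. Only more datasets reduce the random error that comes from averaging over a finite number of imputations. That error grows with the share of information that is missing, so a fixed number of datasets performs worst when much is missing, which is the situation the article reserves for MICE.

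At stake is the reproducibility of the week-52 result. If the p-value lies close to 0.05, a second run of the same program on the same data with another seed could give the other answer. The trial is small and sized near 80% power, so a p-value in that region is not remote.

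**Working it through.** **Inputs from the article.** M = 20 datasets; 34 per arm, 80% power, effect size 0.70, alpha 0.05; 10% dropout; mean changes of 25.2 and 9.53 points and an SD of 26.6.

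**Assumed inputs.** FMI of 0.2 to 0.5 where MICE is used, with 0.1 shown for comparison; complete-data degrees of freedom 68 − 2 = 66; a two-sided test.

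**The plan's own figures.** Twenty is stated without a derivation, so there is nothing to reproduce for it. The sample size does reproduce from the stated effect size: at 0.70 the exact two-sample t-test needs 33.02, rounded up to 34 per arm (power 81.2%), and 68/0.9 = 75.6, hence 76. The article's means and SD give a smaller effect, (25.2 − 9.53)/26.6 = 15.67/26.6 = 0.589, with 67% power at 34 per arm. That is a separate matter; here 0.589 and 0.70 only bracket the calculation.

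**Step 1: efficiency.** Relative efficiency is 1/(1 + FMI/M). At M = 20 it is 0.995, 0.985 and 0.976 for FMI 0.1, 0.3 and 0.5.

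**Step 2: Monte Carlo error of the pooled estimate.** In units of its standard error this is sqrt(FMI/M).

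| FMI | M = 20 | M = 100 | M for error ≤ 0.10 SE (FMI/0.01) |
|---|---|---|---|
| 0.1 | 0.07 | 0.03 | 10 |
| 0.2 | 0.10 | 0.04 | 20 |
| 0.3 | 0.12 | 0.05 | 30 |
| 0.5 | 0.16 | 0.07 | 50 |

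**Step 3: a p-value near 0.05.** Scale the total variance to 1, with between-imputation variance FMI and within-imputation variance 1 − FMI. For each seed, draw the pooled estimate as normal with variance FMI/M about its limit, and the between-imputation variance as scaled chi-square on M − 1 degrees of freedom. Apply Rubin's total variance and Barnard–Rubin degrees of freedom (400,000 draws).

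| FMI | Limiting p = 0.050: middle 95% of seeds, M = 20 | Same, M = 100 | Limiting p = 0.040: chance that p > 0.05, M = 20 | Same, M = 100 |
|---|---|---|---|---|
| 0.1 | 0.036–0.071 | 0.043–0.058 | 12% | 0.3% |
| 0.2 | 0.030–0.085 | 0.040–0.063 | 24% | 4% |
| 0.3 | 0.025–0.099 | 0.037–0.068 | 32% | 9% |
| 0.5 | 0.018–0.127 | 0.032–0.077 | 41% | 19% |

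**Step 4: without selecting borderline results.** Draw whole trials with 34 per arm, so the full-data standardised effect is d × sqrt(34/2), reduced by sqrt(1 − FMI) for missing information. Analyse each trial under two independent seeds and count disagreements about 0.05. For d = 0.589:

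| FMI | M = 20 | M = 100 |
|---|---|---|
| 0.2 | 5.6% | 2.4% |
| 0.3 | 7.5% | 3.2% |
| 0.5 | 10.3% | 4.6% |

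Across d from 0.589 to 0.70 the ranges are about 5 to 11% at M = 20 and 2 to 5% at M = 100. Moving to 100 also gains about 0.5 to 2 points of power and leaves the type I error unchanged.

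**The case against.** The strongest reply is that nothing here is wrong. Rubin's rules at M = 20 are valid: under no effect the type I error matches that of unlimited imputations to within 0.001 for FMI from 0.1 to 0.5, and the efficiency loss is slight. This stands, so the point concerns reproducibility and not bias or error control.

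Second, MICE is only a contingency. The mixed model on available data is the default and has no seed. This also stands: the exposure exists only if the undefined trigger is met.

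Third, the only figure in the article is 10% dropout. At FMI 0.1 the Monte Carlo error is 0.07 standard errors, and a limiting p of 0.03 would cross 0.05 for only 0.4% of seeds. That is true, but missingness near plan might not trigger MICE. Where it is triggered, a larger FMI is plausible, though its size remains an assumption.

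Fourth, seeds and Monte Carlo reporting usually belong in the statistical analysis plan, which is not shown. For the seed that is fair. The number of datasets, however, is a value the article itself states and fixes.

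A reader might also infer something stronger: that the result would change with the seed, or that a quarter or more of reruns would change sides. In simulated datasets with about a quarter to a third missing at week 52, 25% to 29% of reruns at M = 20 did cross 0.05. But those datasets were chosen because their p-value already lay between 0.03 and 0.07, and the missingness rates are not in the documents. The documents do not support that rate for the trial as a whole.

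**Conclusion.** The point holds as a minor one. The article sets a fixed number of imputations for the case in which a fixed number serves least well, and its stated flexibility does not touch that number. A p-value near 0.05 could, not would, change sides. At M = 20 the disagreement between two seeds is about twice that at M = 100 or slightly more.

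These sizes rest on an assumed FMI of 0.2 to 0.5, an effect of 0.589 to 0.70 with 34 per arm, and MICE being used. Seed dependence does not vanish at any finite number, so 100 is a better setting and not a threshold of validity. In the simulated borderline datasets the test statistic still varied between reruns at M = 100, with an SD of 0.053 at about a quarter missing and 0.072 at about a third. The number should therefore be allowed to rise further.

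**What to change.** Replace the sentence that fixes twenty datasets with wording such as: *At least 100 completed datasets will be generated, using a seed fixed before unblinding. The number will be increased if the Monte Carlo error of the week-52 treatment estimate is still material at the observed missingness, and that error will be reported with the result.* What counts as material should be stated as a fraction of the standard error, chosen before unblinding.

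The cost is this wording and a few minutes of computing for 76 participants. Sample size, visits, treatment and the main mixed model are unaffected. Made before unblinding, the change cannot be read as driven by the result.

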**Method:**

Seventy-six participants with KOA will be recruited from the community. We will conduct a single center, parallel group, superiority randomized controlled trial comparing DPT and NS injections, with blinding of physician, participants, outcome assessors and statisticians. Each group will receive injections at week 0, 4, 8 and 16. The primary outcome will be the Western Ontario McMaster University Osteoarthritis Index pain scale (WOMAC), and secondary outcomes include WOMAC composite score, the WOMAC function and stiffness subscale, the Visual Analogue Score of pain, objective physical function tests (the 30 s chair stand, 40- m fast paced walk test, the Timed up and go test) and the EuroQol-5D (EQ-5D). All outcomes will be evaluated at baseline, and 16, 26 and 52 weeks. All analyses will be conducted on an intention-to-treat basis using linear mixed regression models.

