### Eligibility

Eligibility will be screened by a trained research assistant using a phone interview, and potential eligible participants will be invited to meet the principal investigator (a physician) at the study site for confirming eligibility based on the following eligibility criteria:

Inclusion criteria include: (1) age ≥ 45 to ≤75 years old; we set the upper age limit to ensure adequate potential for cartilage regeneration [37]; (2) diagnosis of primary knee OA based on clinical and radiological criteria as defined by the American Rheumatology Association [38]; (3) moderate to severe knee pain for at least 3 months, defined as a score of ≥3 (0–6 ordinal response scale) on the question “What is the average level of your left/right knee pain in the past 3 months?”; and (4) failure to achieve pain reduction to a score < 3 (0–6 ordinal response scale) after 6 months of usual care, such as weight reduction, exercise, physical therapy and pharmacological treatment.

Exclusion Criteria include (1) history of corn allergy [39, 40]; (2) previous knee replacement surgery on the referring knee; (3) pregnancy; (4) body mass index (BMI) ≥ 35 kg/m^2^; (5) patients on anti-coagulant therapy; (6) prior knee injections within 3 months; (7) inflammatory or post-infectious knee arthritis, such as clinically diagnosed rheumatoid arthritis, gouty arthritis, psoriatic arthritis and septic arthritis; (8) significant effusion as defined by a ballotable patella; and (9) co-morbidity or lifestyle preventing participation in the study protocol.

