### Interventions

Following sterile preparation and injection of 1 ml 1% xylocaine as local anesthetic blebs, participants will be injected under ultrasound guidance with 25-gauge needle directed to the suprapatellar pouch using a linear probe with in plane approach. (Fig. 2) An ultrasound guided approach is used as it can guarantee injection into the joint space [46]. The injection procedures will be conducted under aseptic technique [47]. If both knees are painful, only the more painful knee will be injected. Injections will be conducted at week 0, 4, 8 and 16 for both groups. In case of pain flares after injection, the subsequent injection will be commenced after the flare is subsided, or at 1 month. If participants display allergic symptoms to the injected solution, therapy will be terminated but participants will continue to be followed in their allocated group until the end of the study.

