**Fig. 2 Fig2:**
[figure not shown]
Suprapetella pouch injection under USG guidance

Participants in the intervention group will receive injections with loaded syringe containing 5 ml 25% dextrose (D25), prepared by mixing 2.5 ml 50% dextrose with 2.5 ml sterile Water for Injection BP. D25 is a commonly used concentration for intra-articular DPT injection and has been used in previous studies [21, 22]. Participants in the control group will receive injections of 5 ml NS. Recent level one evidence has suggested that NS yields a statistically and clinically meaningful improvement in KOA-related pain up to 6 months after the injection. Therefore, NS will serve as the active control in this trial [48].

Post-injection care: Participants will be observed for 10 min post-intervention consistent with clinical practice and studies [21, 22]. Participants will be advised to take only acetaminophen (500 to 1000 mg every 4 to 6 h as-needed) and avoid non-steroidal anti-inflammatory drugs in the first 48 h after injection, which may interfere with the DPT mechanism of action. They will be allowed to take their usual analgesics medication after 48 h. Participants will be instructed on post-injection care and slow ramp-up of activity. Participants will be contacted 2 days after the injection to assess for side effects.

A home-based post-treatment quadriceps strengthening exercise will be prescribed to both groups and participants will be encouraged to practice daily. Co-interventions will be allowed to both groups, such as conventional medication, physical therapy, acupuncture, herbal medicine, over-the-counter drugs and other active treatments. The use of co-interventions will be retrieved from the Clinical Management System (CMS), an electronic system operated by the Hospital Authority in Hong Kong. Participants will be asked to recall their private treatment as well. However, participants are restricted to receive other injection therapies during the study period.

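### Measurements after undefined post-randomisation events are excluded, so the 52-week comparison is not the intention-to-treat analysis the protocol states

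*Protocol article*

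**What the plan says.** The Abstract (Method) sets the principle for the whole trial: "All analyses will be conducted on an intention-to-treat basis using linear mixed regression models". The Data analysis section spells out what that means: "all available data will be analyzed according to the group they are randomly assigned".

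The last sentence of the same section sets a different rule. It opens "For the patients that meet any of the exclusion criteria such as alternative treatment or severe outcome" and ends by directing that "all subsequent longitudinal measurements since that date of the event will be excluded from the analysis".

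Two other sections bear on the trigger:

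- **Eligibility** lists nine exclusion criteria. Neither alternative treatment nor severe outcome is among them.
- **Interventions** (text after Fig. 2) states: "Co-interventions will be allowed to both groups, such as conventional medication, physical therapy, acupuncture, herbal medicine, over-the-counter drugs and other active treatments". The one limit it sets is that "participants are restricted to receive other injection therapies during the study period".

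The primary aim, at the end of the Background, is knee pain at 52 weeks. Outcomes are collected at baseline and at weeks 16, 26 and 52 (Data collection and management).

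**The concern.** A value recorded after a patient starts another treatment, or after a bad event, is still an available value. Dropping it is a departure from intention to treat as this protocol itself defines it. Because the sentence stands in the only analysis section and is not tied to a secondary analysis, it governs the primary comparison.

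What would be left is closer to a hypothetical effect: the difference had nobody had such an event, estimated by treating the dropped values as missing at random. That may be a legitimate target, but it is not the one announced.

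The triggers are also open to interpretation. The sentence calls them exclusion criteria, yet they are not on that list and are defined nowhere. Whoever prepares the data must decide afterwards whose later measurements count. On the broad reading, care that the protocol permits would cost a patient their later data. Patients still in pain are the likely ones to seek other treatment, so the deletion could depend on outcome and, through outcome, on arm.

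**Working it through.** **1. The contradiction (no arithmetic needed).**

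| Question | Intention-to-treat statement | Exclusion sentence |
|---|---|---|
| Which values enter? | All available | Only those before the event |
| Does a post-randomisation event matter? | No | Yes, it ends the patient's contribution |
| Which analysis? | All analyses (Abstract) | The analysis, with no restriction |

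No other section reconciles the two columns. Measurements before the event stay in the mixed model; only later ones go.

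**2. The trigger.** Alternative treatment, taken plainly, covers acupuncture, herbal medicine and other active treatments, all allowed under Interventions. On a narrow reading it means only the restricted co-treatment (other injections). The text does not settle which.

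**3. Precision.** The planned size reproduces from the stated effect size: effect 0.70, two-sided alpha 0.05 (sidedness assumed) and 80% power give 33.02 by t-test, so 34 per arm; 68/0.9 = 75.6, so 76. With 38 per arm and 10% dropout, 38 × 0.9 = 34.2 remain, with power 81.4%. The protocol gives no event rate, so a range is assumed for the share of remaining week-52 values that the rule deletes:

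| Extra deletion | n per arm | Power at 0.70 |
|---|---|---|
| 0% | 34.2 | 81% |
| 5% | 34.2 × 0.95 = 32.5 | 79% |
| 10% | 34.2 × 0.90 = 30.8 | 77% |
| 20% | 34.2 × 0.80 = 27.4 | 72% |
| 30% | 34.2 × 0.70 = 23.9 | 66% |

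This counts deleted values as wholly lost. Earlier visits in the mixed model would recover part of them.

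**4. Bias (illustration only).** Rates, mechanism and correlations are all assumed. Both simulations use four visits, a true week-52 difference of 0.70 SD and a likelihood-based or GLS fit with group-by-time means.

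- *Correlation 0.5; patients with pain above the pre-treatment mean have the event with probability 0.3, 0.6 or 0.9.* Week-52 values deleted: 10, 20 or 31% in NS and 4, 8 or 12% in DPT. If the event follows pain arising after week 26, the estimate is 0.66, 0.62 or 0.52. If it follows recorded week-26 pain, it is 0.695 to 0.698.
- *AR(1) correlation 0.3 or 0.6; the event occurs above a pain cut-off.* If it depends on the deleted week-52 pain, the estimate is 0.61–0.63 (7% NS and 1% DPT deleted), 0.54–0.58 (16% and 4.5%) or 0.47–0.54 (24% and 8%). If it depends on recorded week-26 pain (16% and 4.5%), the estimate stays at 0.70. With no true difference and the same mechanism in both arms, the bias is within ±0.01.

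**5. A caution on the benchmark.** The figure of 0.70 assumes that the other treatment does not change pain. Suppose it lowers pain by 0.5 SD (an assumption). An analysis keeping all data would then estimate 0.70 − 0.5 × (NS rate − DPT rate):

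- 0.70 − 0.5 × (0.10 − 0.04) = 0.67
- 0.70 − 0.5 × (0.20 − 0.08) = 0.64
- 0.70 − 0.5 × (0.31 − 0.12) = 0.605

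Against 0.66, 0.62 and 0.52 under deletion, the two analyses differ little at the lower rates. The gap from 0.70 is therefore not the error relative to an intention-to-treat estimate.

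**The case against.** The strongest reply is that the sentence is loose shorthand for a few serious protocol departures, such as a non-study injection or knee replacement, and that stopping a patient's data there is a recognised approach. The narrow reading is possible, and a hypothetical target is respectable. But the text does not say so, and even the narrow version is not intention to treat as the protocol defines it. Relabelling the estimate would remove the inconsistency without delivering the effect that was promised.

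The reply is right about several stronger readings that a reader might infer and that the document does not support:

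- *That the rule removes the worst-responding patients.* It removes later measurements, not patients. That those affected are poor responders is a plausible inference, not a stated fact.
- *That it deletes all post-baseline data*, because the study injections would meet "6) prior knee injections within 3 months". That criterion concerns injections before entry; applying it to the trial's own injections is not a sensible reading.
- *That allergy cases are discarded.* For them the protocol says "therapy will be terminated but participants will continue to be followed in their allocated group until the end of the study", and it never classes allergic symptoms as a severe outcome. Continued follow-up also serves safety.
- *That deleted values are then imputed.* MICE is reserved for extensive missing data, and nothing says that excluded values would be imputed.
- *That the bias has a known size or favours one arm.* The simulated cases shrink the difference, arm-specific mechanisms could act otherwise, and no event rate is given. For the same reason it cannot be claimed that the loss exceeds the 10% dropout allowance.

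**Conclusion.** The point holds as an error in what is written. One sentence of the Data analysis section breaks the intention-to-treat definition given earlier in that section and in the Abstract, and it applies to the primary 52-week comparison. Its triggers occur after randomisation, are undefined, do not appear in the Eligibility list and, on plain wording, overlap with allowed co-interventions. This conclusion rests on the text alone.

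The numerical consequence is conditional. Bias is possible if events depend on pain not yet recorded or differ by arm; the 26-week gap between the last two visits leaves room for that. The simulated 0.47 to 0.66 SD (from 0.70) and the power of 79 to 66% are illustrations under assumed rates. Neither size nor direction can be fixed from the document. The matter should be settled before unblinding, because it decides which data enter the primary analysis.

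**What to change.** Remove the exclusion sentence from the primary analysis. State instead that all outcomes observed at weeks 16, 26 and 52 are analysed in the randomised group, whatever the co-intervention, treatment discontinuation or adverse event. Add that outcome assessments continue at the scheduled visits after such events; at present continued follow-up is expressly stated only for patients stopped for allergy.

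If a censored analysis is wanted, keep it as a labelled supplementary analysis. Name its triggering events in advance and reconcile them with the Eligibility list and the co-intervention text under Interventions.

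The cost is mainly wording, since the visits are already scheduled, plus one optional extra analysis and the effort of retaining patients after an event. The downside is that the primary estimate then includes any effect of other treatments that patients receive.
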